**Unlikely:**

There is a temporal relationship to investigational product administration, but there is not a reasonable causal relationship between the investigational product and the AE.

**Possible:**

There is reasonable causal relationship between the investigational product and the AE. Dechallenge information is lacking or unclear.

**Probable:**

There is a reasonable causal relationship between the investigational product and the AE. The event responds to dechallenge. Rechallenge is not required.

**Definite:**

There is a reasonable causal relationship between the investigational product and the AE.

- Action taken
- The outcome of the adverse event – whether the event is resolved or still ongoing.

## **7.5 Reporting Procedure**

### **7.5.1 AEs and SAEs**

All adverse events and serious adverse events will be recorded in the patient's CRF and according to CTCAE (Common Criteria for Adverse Events).

SAEs must be reported within 24 hours after the site has gained knowledge of the SAE. Every SAE must be documented by the investigator on the SAE pages (to be found as part of the CRF). The Serious Adverse Event Report Form must be completed, signed and sent to the medical officer (Head of Department [name]). The initial report shall promptly be followed by detailed, written reports if necessary. The initial and follow-up reports shall identify the trial participants by unique code numbers assigned to the latter.

The medical officer keeps detailed records of all SAEs reported by the investigators and performs an evaluation with respect to causality and expectedness. Based on, among other, SAE reports the sponsor will evaluate whether the risk/benefit ratio associated with study is changed.

### **7.5.2 SUSARs**

SUSARs will be reported to the Competent Authority according to national regulation. The following timelines should be followed:

The sponsor will ensure that all relevant information about suspected serious unexpected adverse reactions that are fatal or life-threatening is recorded and reported as soon as possible to the

Competent Authority in any case no later than seven (7) days after knowledge by the sponsor of such a case, and that relevant follow-up information is subsequently communicated within an additional eight (8) days.

All other suspected serious unexpected adverse reactions will be reported to the Competent Authority concerned as soon as possible but within a maximum of fifteen (15) days of first knowledge by the sponsor.

In order to avoid unnecessary unblinding of study personnel, an independent person at the Clinical Trial Unit at Oslo University Hospital, will unblind before sending to Competent Authority

SUSARs will be reported using the CIOMS form.

Reference Safety Information: No SARs are expected by the sponsor for the purpose of expedited reporting of SUSARs in this clinical trial, i.e. all adverse events that have a reasonable possibility of a causal relationship with the IMP and are “serious” will be reported as SUSARs.

### **7.5.3 Annual Safety Report**

Once a year throughout the clinical trial, the sponsor will provide the Competent Authority with an annual safety report. The format will comply with national requirements.

### **7.5.4 Clinical Study Report**

The adverse events and serious adverse events occurring during the study will be discussed in the safety evaluation part of the Clinical Study Report.

## **7.6 Procedures in Case of Emergency**

The investigator is responsible for assuring that there are procedures and expertise available to cope with emergencies during the study.

In case of emergency, code break will be possible. Closed envelopes with information about IMP will be kept in a locked room at the maternity ward, as described in 9.2.

If a participant experiences a SAE during treatment, unblinding is permissible. Every effort should be made to contact the medical officer before unblinding, unless the SAE is considered to be life threatening.

## **7.7 Data Monitoring Committee (DMC)**

The study will be supervised by an external monitor appointed by The Clinical Trials Unit at Oslo University Hospital. The monitor will perform reviews every 6 months throughout the study period..

## **8 DATA MANAGEMENT AND MONITORING**

### **8.1 Case Report Forms**

For Electronic Case Report Forms (eCRFs)

The Clinical Data Management System (CDMS) used for the eCRF in this study is Epidata. The eCRF system will be FDA Code of Federal Regulations 21 Part 11 compliant.

The designated investigator staff will enter the data required by the protocol into the eCase report forms (eCRF). The Investigator is responsible for assuring that data entered into the eCRF is complete, accurate, and that entry is performed in a timely manner. The signature of the investigator will attest the accuracy of the data on each eCRF. If any assessments are omitted, the reason for such omissions will be noted on the eCRFs. Corrections, with the reason for the corrections will also be recorded.

After database lock, the investigator will receive a digital copy of the participant data for archiving at the investigational site.

### **8.2 Source Data**

Source data are all information in original records and certified copies of original records of clinical findings, observations, or other activities in a clinical trial necessary for the reconstruction and evaluation of the trial. Source data are contained in source documents (original records or certified copies).

The medical records for each patient should contain information which is important for the patient's safety and continued care, and to fulfill the requirement that critical study data should be verifiable.

To achieve this, the medical records of each patient should clearly describe at least:

- That the patient is participating in the study, e.g. by including the enrollment number and the study code or other study identification;
- Date when Informed Consent was obtained from the patient and statement that patient received a copy of the signed and dated Informed Consent;
- Results of all assessments confirming a patient's eligibility for the study;
- Diseases (past and current; both the disease studied and others, as relevant);
- Treatments withdrawn/withheld due to participation in the study;
- Results of assessments performed during the study;
- Treatments given, changes in treatments during the study and the time points for the changes;
- Non-Serious Adverse Events and Serious Adverse Events (if any) including causality assessments;
- Date of, and reason for, discontinuation from study treatment;

- Date of, and reason for, withdrawal from study;
- Additional information according to local regulations and practice.

The records for each participant should contain information which is important for the participant's safety and to fulfill the requirement that critical study data should be verifiable.

### **8.3 Study Monitoring**

The investigator will be visited on a regular basis by the Clinical Study Monitor. For details, please refer to the Monitoring Plan. The Clinical Trials Unit at Oslo University Hospital is responsible for monitoring the study.

### **8.4 Confidentiality**

The investigator shall arrange for the secure retention of the patient identification and the code list. Patient files shall be kept for the maximum period of time permitted by each hospital. The study documentation (CRFs, Site File etc.) shall be retained and stored during the study and for 15 years after study closure. All information concerning the study will be stored in a safe place inaccessible to unauthorized personnel.

### **8.5 Database management**

Data management will be performed by the study group. The Data management procedures will be performed in accordance with NorCRIN guidelines <http://www.norcrin.no/dokumentoversikt/>. The data management process will be described in the study specific data handling plan and the study specific data handling report after database closure.

Data entered into EpiData will be validated as defined in the data validation plan. Validation includes, but is not limited to, validity checks (e.g. range checks), consistency checks and customized checks. A majority of edit checks will be triggered during data entry and will therefore facilitate efficient 'point of entry' data cleaning.

Data management personnel will perform both manual EpiData review and review of additional electronic edit checks to ensure that the data are complete, consistent and reasonable. The electronic edit checks will run continually throughout the course of the study and the issues will be reviewed manually online to determine what action needs to be taken.

Manual queries may be added to the system by clinical data management or study monitor. Clinical data managers and study monitors are able to remotely and proactively monitor the patient eCRFs to improve data quality.

All updates to queried data will be made by authorized study center personnel only and all modifications to the database will be recorded in an audit trail. Once the queries have been resolved, eCRFs will be signed by electronic signature. Any changes to signed eCRFs will be approved and resigned by the Investigator.

Once the full set of eCRFs have been completed and locked, the Sponsor will authorize database lock and all electronic data will be sent to the designated statistician for analysis. Subsequent changes to the database will then be made only by written agreement.

The data will be stored in a dedicated and secured area at Oslo University Hospital. Data will be stored in a de-identified manner, where each study participant is recognisable by his/her unique trial participant number. The data will be stored until 31/12 2035.

## 9 STATISTICAL METHODS AND DATA ANALYSIS

### 9.1 Sample Size calculation

In this study, we will include 250 women.

The sample calculation was based on a randomized controlled trial by Dencker et al from 2009 (37) and a review by Neal et al (27). In the trial, Dencker et al randomized 630 Swedish women who developed slow progress in the first part of active labor. Their inclusion criteria, definitions and time of randomization are similar to what is planned for our study, but they measured the duration from randomization to delivery, in contrast to our scope, which is the duration from IMP is given to delivery. Still, descriptive statistics from their “Early oxytocin group” is important for our sample size calculations. Dencker et al. found that in this group, the mean duration from randomization to delivery was 5.2 hours, SD 2.8 hours. In the review by Neal et al., a total of 17 studies and 7009 nulliparous women were summarized to have a weighted mean duration of labor at 360 minutes (6 hours), and a standard deviation of 216 minutes (3.5 hours). The article states that the mean values “closely parallel those found at median.” Labor duration was calculated from onset of active phase, first stage, with a mean dilatation at start of active phase at 3.7 cm.

Our study will define active labor from 3 cm, and measure the duration from IMP is given to delivery. Since the intervention will not start until a woman crosses the alert line, the duration measured in the planned study, and the corresponding SD, will be expected to be shorter than the total duration and SD reported in Neal et al., which corresponds well to the numbers found in Dencker et al..

A mean difference of 60 minutes in labor duration is considered to be clinically relevant. Such a difference may be assumed to reduce the use of oxytocin, and it is realistic to obtain as all the other studies on spasmolytics found a difference of more than 55 minutes, with a mean difference all studies of 74 minutes.

A methodological issue is that while both the articles we use as a basis for the sample calculations report means and SDs for the duration of labor, this outcome is a time-to-event outcome, with emergency cesarean delivery as a censoring event. The primary outcome will be treated as such in the analyses, and this should also be reflected in the power calculation. However, background data on our primary endpoint are hard to find, and we have therefore based our sample size calculation on the results from Dencker et al.

In the study population, the expected proportion of emergency cesarean delivery will be approximately 7%. Hence, most (approximately 93%) duration times will be observed, and a sample size based on a traditional continuous outcome e.g. a two-sample t-test will give a good indication for the sample size. Due to the inherent skewness of labor duration data, one can expect published values of SD to be slightly overestimated.

With the SD of 2.8 given in Dencker et al., and a power of 80 % we would need in total 246 women (123 women in each group) to discover a difference of 60 minutes. Furthermore, we calculate that

we will need written informed consent from at least 600 women to be able to randomize approximately 250 participants (8% [50 women] will be lost because of elective cesarean section, 25% [140 women] will be induced or receive oxytocin before 3 cm, and 40% [165 women] will not cross the alert line). In addition some of the eligible women will not be randomized because the midwife on duty forget to take the necessary steps and some participants will withdraw from the study.

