Maternal: Common ( $\geq 1/100$  to  $< 1/10$ ): Gastrointestinal: Dryness in the mouth. Cardiology: Tachycardia, dizziness. Ophtalmology: Accomodation disturbance. Unknown frequency: Cardiology: Hypotension, flushing. Skin: Dyshidrosis. Immune system: Anaphylactic shock, anaphylactic reactions, dyspnea, skin reactions including urticarial, rash, erythema and itching. Other forms of hypersensitivity. Kidney: Urinary retention. Ophtalmology: Mydriasis, increased intraocular pressure. Rare cases with serious skin reactions like Steven-Johnsons syndrome have been reported.

According to WHO recommendations for augmentation of labor based on the Cochrane review from 2013 (22),(31), there are 5 RCTs comparing Buscopan with placebo including altogether 845 newborns with no differences in transfer to the Neonatal Intensive Care Unit. One RCT with 100 fetuses did not show any differences in prevalence of fetal distress. One RCT with 130 fetuses did not show any difference in fetal bradycardia, and two RCTs with 230 fetuses did not show any difference in fetal tachycardia. None of the 17 RCTs in the Cochrane review reported any side effects related to Buscopan (22).

Women who are allocated to the control group will contribute to answer an important medical question for future laboring women and their children. They will need an IV access, which could be considered a down side. However, it is routine procedure in the hospital to establish an IV line

when there is labor dystocia. The IV access may be an advantage if they women augmentation with oxytocin or if something unexpected happens.

Women who are allocated to the intervention group may experience a shorter labor if the IMP has the presumed effect. In that case, they will receive less oxytocin, and experience fewer oxytocin side effects. Based on previous studies, the reduction in the active phase of labor will be approximately one hour. This reduction will take place in the first stage (opening phase), and not the second stage of labor (expulsion phase).

Based on data from our department, 72% of primiparous women who crossed the alert line (the inclusion criterion of this study) of the partogram received augmentation with oxytocin with an average duration of 214 minutes. Of the women who crossed the alert line, 15% delivered by cesarean section and 25% had an operative vaginal delivery, compared to 2% and 16% among women with normal progress in labor, respectively.

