### 9.5.1 Primary analysis

This protocol is designed to address a single primary endpoint, which is the duration of labor from when the participant was given IMP, to delivery

This is a time-to-event outcome, where vaginal delivery is the event of interest and emergency cesarean delivery is the censoring event.

The study is designed to establish the superiority of intravenously administered Butylscopolamine bromide compared to placebo on a single primary endpoint; the duration of labor from when the participant was given IMP, to delivery. The null hypothesis is that there is no difference in the duration of labor from when the participant was given IMP, to delivery, between the two treatment groups.

The alternative hypothesis is that there is a difference in the duration of labor from when the participant was given IMP, to delivery, between the two treatment groups.

Superiority of Butylscopolamine bromide on the duration of labor from when the participant was given IMP, to delivery, is claimed if the primary null hypothesis is rejected, and the group difference is in favor of Butylscopolamine bromide.

Statistical significance is claimed if the null hypothesis is rejected on the significance level (alpha) of 0.05 (two-sided). That is, if the p-value of the null hypothesis test is less than or equal to 0.05.

As there is only one identified primary analysis, there will be no adjustments for multiple testing in the secondary analyses. Secondary analyses on secondary endpoints will be regarded as supportive.

The primary endpoint will be analyzed using Weibull regression, and the p-value for the statistical hypothesis test for the primary endpoint will be the p-value from this analysis. Unadjusted Kaplan-Meier plots will be presented. The effect measures will include median (and quartiles) duration in the two treatment groups, and the proportion of women who give birth within 2, 4, 6, 8, 10 and 12

hours after randomization. All efficacy analyses will be presented by the size (point estimate) of the difference between the treatments and the associated 95% confidence interval.

The statistical analyses will be done in SPSS v23, or R version 3.5.0 (<https://www.r-project.org/>).

Robustness of the results will be checked using Cox regression, by including baseline characteristics known to be associated with labor duration as covariates, and performing the analyses with different options for data imputation.

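### The 80% power in section 9.1 belongs to a t-test; the Weibull rule that decides superiority has no stated power, and low censoring does not justify the substitution

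*Protocol*

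**What the plan says.** Section 9.1 takes its inputs from one group of an earlier randomized trial of oxytocin timing, in which "the mean duration from randomization to delivery was 5.2 hours, SD 2.8 hours". It treats 60 minutes as the clinically relevant mean difference and concludes that with this SD and "a power of 80 % we would need in total 246 women (123 women in each group) to discover a difference of 60 minutes". The planned total is 250.

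The section acknowledges that the outcome is time-to-event, that the power calculation ought to reflect this, and that background data are hard to find. It then argues that, with emergency cesarean expected in about 7% and so about 93% of times observed, "a sample size based on a traditional continuous outcome e.g. a two-sample t-test will give a good indication for the sample size".

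Section 9.5.1 sets a different test for the decision: "The primary endpoint will be analyzed using Weibull regression", with the confirmatory p-value taken from that model, vaginal delivery as the event and emergency cesarean as censoring. "Statistical significance is claimed if the null hypothesis is rejected on the significance level (alpha) of 0.05 (two-sided"), and the difference must favor the drug. The protocol reports no power for this rule. It does not say which arm of this trial the 5.2 h stands for, or whether the SD or the distribution's shape is the same in both arms under the alternative.

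**The concern.** The t-test and Weibull regression address different alternatives. The t-test sizing describes an absolute difference in means with one SD. Weibull regression with a treatment covariate assumes a common shape, so that treatment multiplies every duration by one factor (equivalently, a constant hazard ratio). If the drug removes about an hour and leaves the spread unchanged, no single factor describes the effect, and the relative gain is smallest in the longest labors, which weigh heavily in the Weibull fit.

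The share of censored times says nothing about this mismatch. At stake is whether a drug that does what section 9.1 assumes would be missed about one time in five, as printed, or more than one time in three. The planned Cox check is no safeguard: under the common-SD alternative the log-rank test had 63-75% power.

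**Working it through.** **Inputs.** From 9.1: mean 5.2 h, SD 2.8 h, difference 1 h, 123 per arm, 7% censored. From 9.2.1: allocation 1:1. From 9.5.1: two-sided 0.05. Section 1.5 reports 15% cesarean among women crossing the alert line, so 15% is used as a sensitivity value. Not stated, and therefore varied: the SD in each arm, and which arm has the 5.2 h mean.

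**Step 1: reproduce the printed figure.** The standardized difference is 1/(2.8 × √(2/123)) = 2.801, and power = Φ(2.801 − 1.96) = 0.800. The exact t-test gives 0.797. By formula, n = 2 × (1.96 + 0.8416)² × 2.8² = 123.1 per arm. So 246 reproduces, within rounding, as a common-SD t-test size.

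**Step 2: what a common SD implies for Weibull arms.** Matching mean and SD gives shape 1.94 and scale 5.86 h for 5.2 h, and shape 1.53 and scale 4.66 h for 4.2 h. The q-quantile is scale × (−ln(1−q))^(1/shape):

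| Percentile | 5.2 h arm | 4.2 h arm | Ratio |
|---|---|---|---|
| 10th | 1.83 h | 1.07 h | 0.58 |
| 50th | 4.85 h | 3.67 h | 0.76 |
| 90th | 9.02 h | 8.04 h | 0.89 |

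The model needs one ratio throughout. Here it moves toward 1 in the long labors.

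**Step 3: simulate the Weibull rule.** Maximum likelihood, common shape, Wald test at two-sided 0.05 counted only in favor of the drug, 123 per arm, Weibull data, at least 5,000 trials per scenario. The t-test is applied to the full uncensored times; its column is from the 7% runs.

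| Assumed alternative | Shapes | Weibull, 0% censored | 7% | 15% | t-test |
|---|---|---|---|---|---|
| SD 2.8 h in both arms, 5.2 v 4.2 h | 1.94, 1.53 | 62.0% | 64.4% | 63.8% | 79.6% |
| SD 2.8 h in both arms, 6.2 v 5.2 h | 2.35, 1.94 | 63.8% | 63.6% | 61.9% | 80.6% |
| Common shape, 6.2 v 5.2 h, SD 2.8 h in treated | 1.94 | 75.2% | 73.5% | 70.8% | 72.7% |
| Common shape, 5.2 v 4.2 h, root-mean-square SD 2.8 h | 1.74 | 84.4% | 80.3% | 78.4% | 79.9% |
| Common shape, 6.2 v 5.2 h, root-mean-square SD 2.8 h | 2.15 | 84.7% | 82.6% | 78.2% | 80.1% |
| Common shape, 5.2 v 4.2 h, SD 2.8 h in control | 1.94 | 91.0% | 88.2% | 85.4% | 87.5% |

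Other common-SD variants (gamma, lognormal, a pure one-hour shift, other censoring patterns) stay within about 61-67%. With no treatment effect and Weibull data, the rule favors the drug in 2.3-2.7% of trials, near the nominal 2.5%. With gamma or lognormal data the figure was 4.2% and 6.1%, so the power figures for those shapes are, if anything, flattering.

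**Step 4: cross-check the common-shape rows.** Power ≈ Φ(k × ln(mean ratio)/√(2/d) − 1.96), with d = 0.93 × 123 = 114.4 events per arm and √(2/d) = 0.1322.

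- 5.2 v 4.2 h, k = 1.935: 1.935 × 0.2136 = 0.4133; 0.4133/0.1322 = 3.126; Φ(1.166) = 0.878.
- 6.2 v 5.2 h, k = 1.935: 1.935 × 0.1759 = 0.3404; 0.3404/0.1322 = 2.574; Φ(0.614) = 0.730.
- Root-mean-square SD 2.8 h, 5.2 v 4.2 h: control SD 2.8 × √(2/(1 + (4.2/5.2)²)) = 3.08 h, k = 1.741; 1.741 × 0.2136/0.1322 = 2.813; Φ(0.853) = 0.803.

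**Step 5: separate the causes.** Under a common shape, 7% censoring costs about 2 to 4 points. Under a common SD, the Weibull rule is about 14-18 points below the t-test at 0% and 7% censoring alike. The protocol is right that 7% censoring costs little. That fact does not show that the t-test figure carries over.

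**The case against.** The strongest defense is that 61-67% is one end of a range. Section 9.1 gives a single mean and SD from one group of another trial and does not say that 2.8 h persists under treatment. In a t-test sizing, 2.8 h can be the pooled SD; with a common shape that gives 80-83%, essentially the printed figure. A treated SD midway between the common-SD and proportional cases (2.53 h) gives about 76%. The protocol also discloses the approximation and expects published SDs to be slightly too large. It cites an average effect of 74 minutes, at which even the common-SD case reaches about 82%. All of this stands, and it limits the point.

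Three stronger readings are tempting and are not supported.

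- A reader might infer that the Weibull rule has 61-67% power even at its best, because both arms are Weibull in those runs. Equal SDs with unequal means force unequal shapes (1.94 v 1.53), so those runs break the model's common-shape assumption.
- A reader might take section 1.5 to settle that the gain is a fixed hour: "This reduction will take place in the first stage (opening phase), and not the second stage of labor (expulsion phase"). It gives an approximate average and a stage, and does not say whether the saving is fixed or proportional. A simulated proportional effect confined to the first stage (assumed stage means 3.7 and 1.5 h) gave 88%. So it is not the case that the effect must scale with the whole remaining duration to recover 80%.
- A reader might conclude that the primary test must change to restricted mean time. Restricted mean time to 12 h had 77-86% power under a common SD. Under a common shape it had 68% against 73% for Weibull (6.2 v 5.2 h), and 76% against 80-81% (root-mean-square SD).

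What the defense does not rescue is the argument the protocol prints, since the common-SD gap is present with no censoring.

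**Conclusion.** The point holds in this form: the printed 80% is a t-test power, the decision rule is a Weibull p-value with no stated power, and low censoring does not link the two. At 123 per arm, a 60-minute difference and about 7% censoring, Weibull-rule power is:

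- about 61-67% with SD 2.8 h in both arms, 13-19 points below 80%;
- about 73-75% with a common shape, 6.2 v 5.2 h and SD 2.8 h in the treated arm;
- about 80-83% with a common shape and root-mean-square SD 2.8 h;
- about 87-88% with a common shape, 5.2 v 4.2 h and SD 2.8 h in the control arm.

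The common-SD reading is the ordinary one for a t-test sizing and reproduces 246, but the protocol does not state it. The figures assume independent censoring and, for the common-shape rows, Weibull durations. The finding concerns the stated power. It does not show that Weibull regression is an unsuitable primary analysis, or that true power is below 80%.

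**What to change.** In section 9.1:

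1. Delete the claim that low censoring makes the t-test a good indication for the time-to-event analysis.
2. State the assumed alternative: which arm has mean 5.2 h, and whether the SD or the Weibull shape is common to both arms.
3. Replace the 80% with the simulated power of the Weibull rule: about 61-67% for a 60-minute difference with common SD 2.8 h, and about 73-88% under a common shape.

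The cost is wording in 9.1 and the matching text of the separate analysis plan. Section 9.4 allows changes to the plan until database lock. No change in sample size and no extra data are needed.

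Moving the confirmatory test to the mean-time scale, for example restricted mean time from IMP, is an option for the sponsor. It gains power under a common SD and loses power against Weibull regression when the effect is proportional and durations are Weibull. If it is chosen, the horizon must be counted from IMP; the time points now listed in 9.5.1 run from randomization.
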